### 2.6. Retention

The control group does not need incentives to continue in the study since, once their participation is accepted, the data of the mother–child pairs are taken and do not require any other action. The participants of the intervention group, once their participation in the first month’s visit has been accepted, only have to go to the usual health checks until 2 years. At these ages, parents are very receptive to participate in all initiatives that can improve the health of their children, especially if they are developed by the usual professionals. We consider that they will remain in the study without difficulty.

### 2.7. Intervention 

The intervention is being carried out during pregnancy and the following 2 years after birth. The intervention period during pregnancy began, for each individual patient, when they went to their first visit related to the Care Process of Pregnancy, Childbirth and Puerperium Program during the period of time between January 2018 and February 2019. This first visit is carried out by the midwife in charge (Clinical Managing Unit) and is integrated within the standard medical visits and workshops, although reinforced by a specific workshop, purely based on the intervention scheme, at the beginning of the patient’s pregnancy. 

Three workshops take place during this period. They happen once a month for a total of two hours at a time. In each workshop, the patients are handed a fully informed leaflet in which they can learn about the information given and write personal notes at their discretion. 

Workshop number one, specifically created for the intervention period, takes place before the 12th week of pregnancy is reached. To begin the workshop, a 15- to 20-min slideshow is shown to explain the “early programming” concept and its close relation to childhood obesity. Immediately after this, the attendees will be fully informed about the importance of physical exercise, quitting toxic habits and creating a healthy eating plan for the entire family. 

At the second workshop, which has to be completed between the 16th and 18th weeks of pregnancy, the information provided is related to the specific healthcare and healthy habits that a pregnant woman should embrace, considering the changes she will experience.

Finally, on the third workshop, carried out between the 30th and 32nd weeks of pregnancy, the attendees will learn about the special characteristics of care related to newborns. To begin, a 20-min slideshow, in which the postnatal programming and its different factors are explained in detail, will be shown. After that, exclusive breast feeding will be explained and promoted as the preferable option. The child and adolescent health scheme planed by the Andalusian health authorities will also be introduced during this session. 

The first visit within the pregnancy, birth and puerperium scheme is carried out between the 4th and 7th week of pregnancy. It is a 30-min visit in which the pregnant woman will receive an informative leaflet with general recommendations about a healthy pregnancy, where she will be introduced to the concept of early programming and its close relation to childhood obesity. Those pregnant women considered obese, who admit smoking, or who are believed to be unhealthy dieters, will be encouraged to take on the first workshop. 

Subsequent visits will monitor the risk factors, including whether new factors arise or persist, in which case workshop number one will be offered again or as a first time informative session. Early programming and childhood obesity will be the main and consistent ideas to be reinforced on each visit. The basic recommendations and lifestyle habits proposed to each pregnant woman will be related to these core concepts. 

Both workshops two and three will be offered to all pregnant women in the program. Those in the 14th–16th week of pregnancy will be encouraged to attend workshop number two, and those in the 30th-32nd week will be offered workshop number three.

Recommendations during the first year:Promotion of breastfeeding (exclusively up to 6 months).Participation in local breastfeeding support groups.Avoidance of active/passive maternal smoking.Information on the advantages of breastfeeding for the prevention of childhood obesity.Recommendations for artificial lactation:Formulas with lower protein content are recommended up to 12 months, with a strong recommendation for children of overweight or obese mothers, gestational diabetes, and macrosomic newborns, if breastfeeding is not possible.Introduce complementary feeding between 4 and 6 months of life.Bottle feed should be slow, at least 15-20 min.Supplementary feeding tips:Reduce the protein content of animal origin between 6-12 months: 15 g/day of meat at 6 months and increase up to 40 g/day at the end of the first year.Tips to facilitate the introduction of fruits and vegetables to favor a more varied diet in the preschool stageAvoid the introduction of sweet flavors: honey, infusions, juices, etc.Tips for developing self-regulation of appetite/satiety.Identify signs of appetite/satiety in the infant.Do not force eating.Do not calm crying or night awakenings systematically with food.Vitamin D supplement (400 IU/day) during the first year.Tips for developing a secure attachment.Tips to develop adequate sleep habits.Recommendation of active play after 6 months.Avoid using screens, especially for sleeping and during meals.

Recommendations during the second year:Recommend growth formulas because of their lower protein content, compared to cows’ milk.Limit milk intake to about 500 mL per day.Restrict the intake of sweet flavors.Restrict the bottle as soon as possible.Maintain the recommendations in items 7–9 of the first year.

Most of the recommendations proposed in the intervention are not novel themselves, except for the recommendation to feed formulas with lower protein content to infants who are not breastfeeding. 

The strength of the intervention is given by: The coordinated action of all professionals who attend pregnancy and the first 2 years of postnatal life, offering recommendations about healthy lifestyles, guidelines on suitable nutrition and proper acquisition of habits. Using the concept of early programming as an opportunity for primary prevention of obesity and other chronic diseases.The use of the concept of early programming as the central axis of the intervention, associated with an opportunity to carry out a primary prevention of obesity and other chronic diseases.Explaining to the families, in this stage of great receptivity to the recommendations on health care, that the care guidelines for your children can have permanent and long-term consequences on their health.

### 2.8. Measures and Outcomes

#### 2.8.1. Independent Variables 

Weight gain during pregnancy. The difference in maternal weight between the first visit (weeks 4–7) and the last one (week 38) is calculated. If the weight on the last visit is not registered, it is calculated with the final pregnancy weight recorded in the hospital discharge report. It will be classified as adequate or excessive according to the accepted values of weight increase by the pre-gestational body mass index (BMI) of the Institute of Medicine (IOM) and National Research Council [61].Mother’s body mass index (BMI) at the first visit (weeks 4−7). This will be evaluated as a continuous measure.Maternal nutritional status. Classified as obesity, overweight, normal weight or low weight.Maternal smoking during pregnancy. Active smoker, passive smoker and non-smoker. The mother is considered an active smoker if she consumes any amount of tobacco.Gestational diabetes.Caesarean section.Newborn sex.Newborn weight. Registered in hospital visit (newborn measures).Duration of exclusive breastfeeding. Full months of exclusive breastfeeding are considered.Weight gain in the first four months. The difference in the infant’s weight between birth weight and fourth-month-postnatal weight at the visit is calculated as grams/day. As secondary outcomes, weight gain in the first six months and in the first year are also calculated.Introduction of complementary food, before or after 4 months of age.Vitamin D supplementation (400 IU/day) in the first year. Full months of supplementation are considered.Type of milk in second year. Classified according to the type of milk that was consumed the largest number of months: breastfeeding, growing milk or cow milk.BMI at 1 year of life.

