### 2.4. Recruitment

A single midwife will take charge of maternal education in the CMU Puerto Real, which includes the Ribera del Muelle Health Centre where there are three paediatricians, and the Rio San Pedro Health Centre where there is one. Therefore, all pregnant women will receive exactly the same information about the intervention. After birth, the parents will decide in which of the six paediatricians of the BHZ of Puerto Real they will register their children, and we cannot interfere in that decision.

The study population of the control group will be constituted by two-year-old children of two quotas of the Basic Health Zone of Puerto Real. The paediatricians have employment stability for at least the expected duration of the study and have agreed to participate. The inclusion in the study and the data collection will be carried out in the health controls at 2 years of age at the same time as the intervention in pregnant women begins, so that neither mothers during pregnancy nor infants after delivery will have been influenced by the intervention. Once the intervention ends, their results will be analyzed from the data obtained from the mother–child pairs.

Following the above criteria, all newborns assigned to the four pediatricians of the unit that meet the inclusion criteria will be included in the intervention group. Two paediatricians from the same unit will also participate in the data collection for the control group. Including a greater number of pediatricians is necessary to obtain the calculated sample of the intervention group, due to the decrease in the birth rate observed in recent years. Inclusion in the study will be done at the first pediatric visit of the newborn.

The inclusion criteria are: two-year-old infants whose pregnancy begins in the 14 months following the start of the intervention, and whose mothers have made the complete follow-up of their pregnancy in the Care Process of Pregnancy Childbirth and Puerperium and begun the monitoring of child health controls of the Andalusian Children and Adolescents Health Program in our unit. The exclusion criteria are: infants whose parents do not authorize their participation in the study in writing.

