### 2.9. Data Collection 

The data for the control group will be collected through a data collection sheet, specifically designed for the study, from three sources: (1)Direct questions to the parents at the one-year and two-year visits, performed by paediatricians.(2)The weight, height and BMI records of the Diraya program, both for pregnant women and children.(3)Mothers and children’s medical records from the Diraya program. The form will be subsequently computerized.

The data for the intervention group will be collected in the same way, but also at the newborn and six-month visits, developed by paediatricians.

The midwives in the usual CPPCP controls will collect the gestational and delivery variables. Nurses and paediatricians in the usual controls of the A-CAHP will collect the somatometric variables of newborns up to 2 years.

After childbirth, during the puerperal visit, the midwife will register the birth data in the Diraya program as a hospital visit. If the mother does not attend the puerperal visit, it will be the paediatricians at the newborn visit who will collect the data from birth.

The weight and height of pregnant women will be measured with an ADE (GmbH & Co, Hamburg, Germany) scale, model M304641-01, with a reading range from 2 to 250 kg and a precision of 100 g, with an ADE stadiometer coupled to the scale, model MZ10023-1, with a reading range of 60–210 cm and a precision of 0.1 cm.

Weights will be measured in the first and second year of age with the child naked on a Soehnle baby scale, reading in a range of 0–20 kg with a 10 g precision. The length will be measured with the infant in supine position with a rigid Añó-Sayol stadiometer, with a reading range of 25 to 90 cm and an accuracy of 0.5 cm. The tables of weight, length and BMI values of the WHO will be used.

The skin folds will be measured with a Holtain Skinfold Caliper plicometer with an amplitude of 0–46 mm, 0.2 mm graduation and a constant pressure of 10 g/mm^2^. They will be measured in the left side of the body, in triplicate and by a single observer for each pediatric quote, according to universally recommended techniques [62,63].

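### Birth weight and early weight gain are modelled without gestational age, so their coefficients in the factor model mix prematurity with fetal size and postnatal growth

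*Protocol article*

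**What the plan says.** Section 2.8.1 of the protocol article lists 14 independent variables. Birth size enters as an absolute weight: "Newborn weight. Registered in hospital visit (newborn measures". Early growth is the difference "between birth weight and fourth-month-postnatal weight at the visit is calculated as grams/day", and "weight gain in the first six months and in the first year are also calculated". Gestational age at birth, preterm status, size for gestational age and corrected age are not in the list, and no other section mentions them.

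On eligibility, section 2.4 gives one ground for exclusion: "The exclusion criteria are: infants whose parents do not authorize their participation in the study in writing". Its inclusion criteria cover the conception window, pregnancy follow-up and the start of child health controls in the unit. They set no limit on gestational age or on multiple birth, and "all newborns assigned to the four pediatricians of the unit that meet the inclusion criteria will be included in the intervention group".

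Section 2.10 then relates the dependent variables (BMI and percentage fat mass at 2 years) to the independent variables by a generalized linear model. Section 2.9 says that "The midwives in the usual CPPCP controls will collect the gestational and delivery variables", without saying which variables these are.

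**The concern.** A preterm baby of normal size for its gestation and a growth-restricted term baby can have the same birth weight. Raw weight gives them the same value, and nothing else in the list tells them apart. Gain in g/day is counted from the date of birth, so in a preterm infant it covers an earlier stretch of growth than in a term infant.

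The interpretation of individual factors is at stake. The Introduction names rapid weight gain in the first year as a programming factor, and section 2.7 gives specific advice for macrosomic newborns. A reader will want to know how birth size and early gain relate to fatness at 2 years. As specified, those coefficients carry an unknown amount of prematurity.

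**Working it through.** The article states no figure on this point, so there is none to reproduce. The text was checked first. The size of the effect was then illustrated with assumed inputs.

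**1. Can preterm children enter?** Section 2.4 requires mothers "whose mothers have made the complete follow-up of their pregnancy in the Care Process of Pregnancy Childbirth and Puerperium", which might remove some very early births in practice but sets no gestational limit. Section 2.8.1 places the last maternal weight at week 38, with a fallback: "If the weight on the last visit is not registered, it is calculated with the final pregnancy weight recorded in the hospital discharge report". A birth before week 38 therefore stays in. Neither section mentions multiple births.

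**2. Attenuation of the birth-weight slope.** Write birth weight as (slope × gestational age) + residual, where the residual is size for gestational age. If the outcome depends only on the residual, leaving out gestational age shrinks the birth-weight slope by the share of birth-weight variance due to gestational age:

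share = (slope × SD of gestational age)² / [(slope × SD of gestational age)² + residual SD²]

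All inputs below are assumptions.

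| Slope (g/week) | SD of gestational age (weeks) | Residual SD (g) | Calculation | Share |
|---|---|---|---|---|
| 120 | 1.5 | 430 | 32,400 / (32,400 + 184,900) | 0.15 |
| 150 | 1.8 | 420 | 72,900 / (72,900 + 176,400) | 0.29 |
| 180 | 2.0 | 400 | 129,600 / (129,600 + 160,000) | 0.45 |

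**3. Second illustration, by simulation.** Assumed inputs: 170 g per week, size-for-age SD of 12.5% of the expected weight, and an outcome driven only by size for gestational age. Slopes are per 425 g.

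| Preterm share | Slope without gestational age | Slope with it | Ratio |
|---|---|---|---|
| 4% | 0.746 | 1.004 | 0.74 |
| 7% | 0.692 | 1.010 | 0.68 |
| 10% | 0.647 | 1.016 | 0.64 |

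The shrinkage is 26–36%, inside the 15–45% range. This is not independent evidence, because the simulation makes the same key assumption about what drives the outcome.

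**4. The group contrast.** Section 2.5 gives 100 controls and 150 intervention children with 15% loss: 100 × 0.85 = 85 and 150 × 0.85 = 127.5, say 128, or 213 in all. At an assumed 7% preterm, that is about 0.07 × 213 = 15 children. The chance SD of the between-group difference in preterm share is

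√[0.07 × 0.93 × (1/85 + 1/128)] = √0.00127 = 0.036.

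Section 2.5 does not say whether 100 and 150 are before or after losses. If after, the figure is √[0.0651 × (1/100 + 1/150)] = 0.033. Even if preterm and term children differed by a full SD in fatness, a one-SD chance imbalance would move the group difference by about 0.036 × 1 = 0.04 SD.

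**5. Early gain.** No calculation was made for this coefficient. The direction and size of any distortion depend on how preterm infants grow in these cohorts, and the article gives no data on that.

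**The case against.** The strongest objection is that the project's aim and hypothesis concern the control-versus-intervention comparison of body fat at 2 years, which step 4 shows is barely touched by chance imbalance. That stands. A reader might infer that the main comparison is biased, but the document does not support that. A material effect would need a systematic difference in preterm share between the cohorts. That is possible with a historical control, but nothing in the article shows it.

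Four further objections stand in whole or in part.

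- The Introduction's list of programming factors includes rapid first-year gain but not birth weight. Newborn weight is one covariate among 14, so calling birth size central to the programming hypothesis would overstate it.
- The attenuation is conditional. If the intended quantity is the association with actual birth weight, whatever its cause, leaving out gestational age is not an error. The article does not say which is intended.
- It is tempting to say that the team could not check whether the groups differ in preterm share. Section 2.9 does not support this: medical records of mothers and children are a source for both groups, so the share can be recovered.
- Standardising birth weight does nothing for the gain variable. With early gain and BMI at 1 year in the same model, the birth-weight coefficient is not a clean birth-size effect even after gestational age is added.

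One might also say that a condensed article leaves such detail to a fuller document. That is true of a sensitivity analysis but carries less weight for the variable list. The list is operational, with units, category rules and fallbacks, and section 2.10 builds the model on it.

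**Conclusion.** The point holds for the secondary factor model. As written, the model cannot separate prematurity from fetal size in the birth-weight coefficient, or from postnatal growth in the early-gain coefficient. If fatness at 2 years follows size for gestational age, the raw birth-weight slope is too small by roughly 15–45%. Every input to that range is assumed. The distortion of the gain coefficient is plausible but unquantified. The effect on the group contrast from chance imbalance is a few hundredths of an SD. The change is worth making because it is cheap and improves the interpretation of the factors; the main comparison does not depend on it.

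**What to change.** - Add gestational age at birth to section 2.8.1, taken from the existing birth records in both groups.
- In the factor model, use birth weight standardised for gestational age and sex. Where early gain is modelled, include gestational age or use age-corrected gain.
- Report the preterm share by group.
- Repeat the factor model and the group comparison in term singletons, as a sensitivity analysis only.
- Do not adjust the group effect for gestational age. The intervention starts in pregnancy and may act on it, so adjustment could remove part of the effect. Restriction to term births has a similar weakness, which is why it should not be the main analysis.

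The cost is one extra field per child and one additional analysis. The sensitivity set would lose about 15 of 213 children at an assumed 7% preterm, plus term multiple births, for which the article gives no rate. No visit or element of care changes.

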Postnatal: short breastfeeding [44], rapid weight gain in the first year of life [45], excess protein intake [5,46], vitamin D deficiency [47,48], and caesarean section (where there is evidence for and against) [49,50,51].

Other factors, related to lifestyle and family eating behaviors, have also been linked to an increased risk of obesity in childhood: appetite control [52,53], sleeping habits [54], quality of maternal-child relationship [55] and other modifiable factors like screen time, physical activity [56], complementary feeding [57], etc. 

The accumulation of these early programming factors in the same individual is associated with a progressive risk of obesity at 6 years old [58,59] or at 7–10 years old [60], regardless of what these factors are. Although all factors that are associated with childhood obesity cannot be controlled, the decrease in the number of factors that accumulate in an individual could reduce the obesity risk.

Accordingly, prevention strategies are more effective the earlier they have been developed in the life course. Therefore, we have developed strategies that are implemented from the prenatal stage until 2 years old. The concept of early programming must be used alongside the prevention opportunity, with a positive message that obesity prevention is possible by decreasing the number of programming factors. In this project, we want to carry out a realistic intervention, developed entirely in primary care by the usual health team. It must be acceptable to primary care professionals and supported and endowed with resources by the health administration. It also must be integrated into the routine practice of the Andalusian Children and Adolescents Health Program (A-CAHP) and Care Process of Pregnancy, Childbirth and Puerperium (CPPCP) controls, taking advantage of the high number of visits planned in these programs, so that it can, if proves to be effective, generalize to routine activity in primary care. 

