#### 2.8.2. Dependent Variables

BMI at 2 years of life.Percentage of fat mass at 2 years of life.

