### 2.10. Data Analysis

For the statistical analysis of these data, the statistical program SPSS Version 22 software (IBM Corp, Armonk, NY, USA, 2015) will be used:

Descriptive analysis. The means and standard deviations for the quantitative variables and the absolute and relative frequencies for the qualitative ones will be determined.

Bivariate analysis. The Kolgomorov–Smirnov test will be used to determine if the quantitative variables are parametric; when the sample is less than 50, the Shapiro–Wilk test will be used. For the comparison of the dependent variables with qualitative independent ones, we will use the Student’s *t*-test and ANOVA for independent means as a test of statistical significance, and the Mann–Whitney U and the Kruskall–Wallis tests for the nonparametric ones. For independent quantitative variables, the Pearson and Spearman coefficients will be used.

Multivariate analysis. The analysis of the degree dependent variables with the independent variables will be carried out using the generalized linear model. For the linear regression, we will use the Gaussian family and as a function of the identity bond and for the binary logistic regression, the binomial family and the logit link function.

To detect differences, a significance level *p* < 0.05 will be used and the 95% confidence intervals will be calculated.

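### Weight gain to 6 months and to 1 year is called a secondary outcome but listed only as an independent variable, so as written it gets no group comparison and may absorb part of the intervention effect

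*Protocol article*

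**What the plan says.** The protocol article treats infant weight gain in section 2.8.1, among the independent variables. One list item defines gain over the first four months: "The difference in the infant’s weight between birth weight and fourth-month-postnatal weight at the visit is calculated as grams/day". The same item continues: "As secondary outcomes, weight gain in the first six months and in the first year are also calculated". This is the only place where the article calls anything a secondary outcome.

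Section 2.8.2 gives the full list of dependent variables: "BMI at 2 years of life.Percentage of fat mass at 2 years of life". No weight gain appears there.

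Section 2.10 has two inferential steps, both built on the division made in section 2.8. The bivariate step begins: "For the comparison of the dependent variables with qualitative independent ones, we will use the Student’s" t-test, with ANOVA, rank tests and correlation coefficients for the other cases. The multivariate step reads: "The analysis of the degree dependent variables with the independent variables will be carried out using the generalized linear model". The descriptive step covers quantitative variables in general.

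**The concern.** A variable named as an outcome should be compared between the groups. One filed only as an independent variable is used to explain something else. The article does both with the 6- and 12-month gains and then ties every test and model to the filing, not to the name. Two things are at stake.

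- **A missing comparison.** The hypothesis in section 1 is that the intervention reduces the early programming factors a child accumulates. The Introduction lists "rapid weight gain in the first year of life" among them. Whether the groups differ in first-year gain therefore tests a step in the trial's own argument, and section 2.10 as written does not make that test.
- **A distorted comparison.** The intervention starts at the first pregnancy visit, so gain to 6 or 12 months comes after it. If such a variable stands beside study group in the model for 2-year BMI or fat mass, the group coefficient no longer measures the whole effect of the intervention.

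The unclear role also leaves room to decide after seeing the data whether the gains are outcomes or covariates.

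**Working it through.** The plan attaches no figure to this point, so the check is mainly a comparison of sections.

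**1. Role of the gains to 6 months and 1 year**

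| Place | Role |
|---|---|
| 2.8.1, wording | Secondary outcomes |
| 2.8.1, section title | Independent variables |
| 2.8.2 | Not listed |
| 2.10, bivariate | Only dependent against independent variables |
| 2.10, multivariate | Only dependent modelled on independent variables |

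The wording and the filing conflict, and section 2.10 follows the filing. What remains for the gains is description and use as predictors.

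**2. Effect of using them as predictors**

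Assume study group is in the model. Section 2.8.1 does not list it, but the third specific objective in section 1 is to compare the groups. Let *G* be group (1 = intervention), *M* weight gain and *Y* the 2-year outcome, with the same other covariates throughout. For the Gaussian model with identity link named in section 2.10:

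- M = a₀ + a·G
- Y = c₀ + c·G, where c is the total group effect
- Y = d₀ + c′·G + b·M, where c′ is the group coefficient adjusted for gain

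Least squares gives c = c′ + a·b, so c′ = c − a·b. The shift is zero only if the groups do not differ in gain (a = 0) or gain is unrelated to the outcome given group (b = 0). The protocol's hypothesis implies a < 0 (less rapid gain with the intervention) and b > 0 (rapid gain goes with more fat). Then a·b < 0, and c′ is less negative than c: the benefit looks smaller than it is. The documents give neither a nor b, so the shift cannot be put in figures. Common causes of gain and later fatness could also bias b in either direction. The identity is exact only for the linear model, not the logistic one.

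**3. Would a group comparison of gain be informative?**

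Inputs from section 2.5: 100 controls, 150 intervention children, α = 0.05, 15% loss. Power of 80% is an assumed convention, as the article states none. The detectable standardised difference is (1.960 + 0.842) × √(1/n₁ + 1/n₂), unadjusted:

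- 100 v 150: 2.802 × √(0.01000 + 0.00667) = 2.802 × 0.1291 = 0.36 SD
- after loss, 100 × 0.85 = 85 and 150 × 0.85 = 127.5, taken as 128: 2.802 × √(0.01176 + 0.00781) = 2.802 × 0.1399 = 0.39 SD

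These values hold for any continuous variable at these group sizes. They show that the comparison is feasible, not how much harm its absence does.

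**4. Are the data there?**

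Section 2.9 gives both groups a one-year visit and draws weights from the Diraya records. The six-month collection visit is described for the intervention group only, so six-month weights in controls depend on routine records.

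**The case against.** The best counter-argument is that the phrase is loose. It sits inside one item on infant weight gain and may mean only that two further versions of that predictor are computed. None of the three specific objectives mentions weight gain; all concern body fat at 2 years. On that reading no outcome analysis is missing and the label needs correcting. This is plausible, and the fix allows for it. It does not remove the second problem: a predictor measured after the intervention began still does not belong in the model that estimates the group effect.

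It can also be said that an article leaves the handling of secondary variables to an analysis plan. That excuses missing detail, but not a variable given two incompatible roles in the current text.

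A reader might infer more than the documents support:

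- **That the four-month window cannot register the feeding advice.** Section 2.7 says "Introduce complementary feeding between 4 and 6 months of life" and "Reduce the protein content of animal origin between 6-12 months", but these are ages for the food, not for the visit at which advice is given. The third workshop, at weeks 30 to 32 of pregnancy, already covers postnatal programming. Breastfeeding and formula advice act within the first four months, and the 6- and 12-month gains in the same item span the later period. Four months is listed first but nowhere called the main window.
- **That the article defines weight gain in conflicting ways.** The Introduction lists published risk factors; only section 2.8.1 defines the variable, and it includes the first year.
- **That first-year gain is the earliest growth outcome open to change.** Newborn weight and four-month gain come sooner.
- **That the information is lost.** The gains are calculated and can be described. What is absent is a planned group comparison.

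**Conclusion.** The point holds as a contradiction in the stated analysis. Both variables the article names as secondary outcomes lack a between-group comparison as written. Both are also placed where they may absorb part of the group effect on 2-year BMI and fat mass.

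The first part rests on the text of sections 2.8.1, 2.8.2 and 2.10 alone. The second assumes that study group and the gains enter the same model, that the intervention affects gain, and that gain relates to the 2-year outcomes. The last two are the protocol's own hypothesis. The size of the shift is unknown.

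This should be corrected, but it does not invalidate the main comparison of fat mass, which can be made without these gains.

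**What to change.** 1. Give the gains one role. If they are outcomes, list weight gain from birth to 12 months in section 2.8.2 as a secondary dependent variable. Add gain to 6 months where routine records supply it for controls.
2. For each, report the control-intervention difference with its 95% CI, adjusted for infant sex and for maternal characteristics fixed at or before the first visit, such as first-visit BMI. Do not adjust for birth weight, which the prenatal intervention can affect.
3. State that these gains are left out of the model that estimates the group effect on BMI and fat mass at 2 years. A separate model, labelled as such, may still study them as early programming factors.
4. If they were only ever meant as predictors, delete the outcome label in section 2.8.1 and keep step 3.

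The cost is a few lines in sections 2.8 and 2.10 and one regression per variable. Gain to 12 months needs no new data collection. Gain to 6 months depends on how complete the controls' routine records are. The downside is two more comparisons, to be labelled secondary.
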